## Abstract

**Background:**

In order to manage the acute and long-term effects of living with a chronic disease such as diabetes, both medical treatment and good psychosocial support are needed. In this study, we wish to examine whether a psychological group intervention targeting people with poorly controlled type 1 diabetes can be helpful in augmenting quality of life while also lowering participants’ HbA1c level. The group intervention will consist of a brief treatment developed from a branch of cognitive behavioural therapy called acceptance and commitment therapy, which is part of the so-called third wave of cognitive behavioural therapy. Common for these third-wave therapies, the focus is less on the content and restructuring of thoughts and more on the function of behaviour. Here, we describe the protocol and plans for study enrolment.

**Methods/Design:**

This on-going study is designed as a randomised wait-list controlled trial. Eighty patients aged 26–55 years and with an HbA1c level >70 mmol/mol at the time of enrolment will be included.

**Discussion:**

In this study, we will assess the effect of starting acceptance and commitment therapy group treatment for patients with type 1 diabetes and its effect on glycaemic control and well-being.

**Trial registration:**

Current controlled trials: ISRCTN17006837, registered 12^th^ January 2015

**Electronic supplementary material:**

The online version of this article (doi:10.1186/s12912-015-0101-y) contains supplementary material, which is available to authorized users.

## Background

The role of nursing, psychology and behaviour medicine in the management of diabetes has gained increasing attention in the past decade, but the field is still young and rather narrow in scope [1–3]. Some of the progress made in diabetes treatment has helped to ease the burden of living with diabetes, while some of the advances have also called for more intensive and demanding self-care [4, 5]. In order to manage both the acute and long-term effects of living with a chronic disease such as diabetes, both medical treatment and good psychosocial support are needed [6].

Among patients with diabetes, psychiatric co-morbidity is associated with poorer glycaemic control [7, 8] and contributes (along with genetic variation and other stress factors) to why so few patients with diabetes reach glycaemic control goals. People with diabetes are two to four times more likely to be diagnosed with depression than those without the disease [4, 9–11]. The repetitive practical and emotional burdens that often accompany the self-management of diabetes play an important role in the increased risk of depression [12].

### Acceptance and commitment therapy

Acceptance and commitment therapy (ACT) is part of the so-called third wave of cognitive behavioural therapy (CBT). Common to these third-wave therapies, focus is less on the content and restructuring of thoughts and more on the function of behaviour. In practise, these therapies focus on teaching patients skills of coping and empowerment, such as strategies of acceptance and mindfulness [13].

The theoretical background of ACT is based on functional contextualistic philosophy of science and modern learning theory, mainly relational frame theory and contextual behavioural science. Both theories strive to understand human behaviour and language from its context and use this knowledge to predict and influence behaviour. ACT can be seen as a unified model of behavioural change, rather than a specific set of methods or techniques [13].

Similar to CBT, ACT acknowledges the relevance of language and cognition in psychopathology and psychotherapy, but ACT does not consider thoughts and beliefs to directly cause other behaviours. Therefore, it is seen as unnecessary to target the content of thoughts in order to promote behavioural change. Instead, thoughts are valued the most for their usefulness in achieving a more valued life [13].

From an ACT perspective, psychological and physical pain is unavoidable and a natural part of the human condition—sickness, death, separation and other large and small disappointments are bound to happen to us if we lead a life that matters to us. While pain might be part of the human condition, suffering does not have to be.

Suffering is considered to be caused by our ability through language to categorise, predict, evaluate, reminisce about the past and worry about things yet to come. Since this stance of accepting pain can be provocative for some patients, it is important in treatment to emphasise that accepting pain is not a passive state but a proactive stance that focuses on behaving in ways that lead to better health and quality of life (QoL).

Accepting the inevitability of pain and struggle, including physical illness and distress, is the first step towards psychological flexibility. The overarching goal in a treatment using ACT is thus to increase patients’ psychological flexibility concerning thoughts, feelings and behaviour. Psychological flexibility is the ability to accept one’s own difficult feelings and thoughts while at the same time striving to live a meaningful life according to one’s personal values [13]. Thus, psychological flexibility involves adjusting behaviour according to the current situation in a helpful manner and not by the ebb and flow of thoughts and emotions. The opposite, psychological inflexibility, can include sticking to a behaviour and mind-set even though it continues to create suffering. Psychological inflexibility is often manifested as emotional avoidance, i.e., the attempt to avoid or ignore unpleasant thoughts, emotions and situations. In ACT, emotional avoidance is seen as the main reason why humans suffer from psychological illness. This emotional avoidance can take many forms, such as avoidance of close relationships, distractions such as excessive game playing, binge eating and the use of drugs or alcohol. These strategies are negatively reinforced as they offer somewhat temporary relief from unpleasant experiences.

Experiential avoidance is not negative per se, but often becomes a problem when it leads to psychological inflexibility and stands in the way of leading a rich and valued life [14].

The ACT model of psychological flexibility is based upon six core processes: acceptance, verbal defusion, mindfulness, self-as-context, values and committed action. In therapy, these processes are targeted through exercises and values clarification. As ACT is a behavioural therapy, the focus lies in experience-based learning, both in-session and as committed actions to try in-between sessions. In summary, experiential avoidance and psychological inflexibility may be important factors in many diabetes patients’ struggle with self-care. Avoidance can make a person ignore recommendations or behave in ways that are not helpful, such as not monitoring blood sugar levels. Inflexibility may manifest as resistance to change and difficulties in adapting to new circumstances. Helping patients to improve in these factors may thus help improve self-care and health.

### Empirical evidence

The current empirical evidence for ACT is rapidly emerging, but is still not as sound as the evidence for CBT. ACT is approved as evidence-based practice for the treatment of depression and chronic pain by the American Psychological Association. Other areas for implementation are also being considered [15] ACT has been tested in numerous behavioural medicine areas such as pain [16], chronic physical diseases [17] and obesity [18, 19], with data showing preliminary good results.

The Swedish institute for assessing health care interventions, SBU, issued a report on diabetes care in 2009 in which they stated that more studies were needed in order to assess the effectiveness of CBT and other interventions for individuals with type 1 diabetes [20]. In a Swedish randomised controlled trial, Amsberg et al. [21] tested the effectiveness of CBT (primarily administered in a group setting) in patients with diabetes. The study specifically aimed at maintaining behaviour change, as previous studies have shown that improvements made directly post-treatment are rarely maintained during follow-up. In the study, the 40 participants in the intervention group significantly improved regarding glycaemic control as measured by HbA1c level, diabetes-related distress, well-being, perceived stress, anxiety and depression, as well as frequency in self-monitoring of blood glucose in comparison to the control group.

To date, there has only been one study testing the effectiveness of ACT in a diabetes population of patients with type 2 diabetes. The study randomly allocated 81 patients to either a control group (in which participants received education about how to manage their diabetes) or to an ACT intervention. Participants in the ACT intervention group received the same education, as well as a 1-day ACT workshop, where the participants were taught how to apply mindfulness and acceptance skills to difficult thoughts and emotions. After 3 months, the participants in the ACT group were more likely to use these coping strategies and reported better diabetes self-care as well as having an HbA1c value in the target range [22].

### Study aim

For this study, we wish to examine whether a psychological group intervention targeting people with poorly controlled type 1 diabetes can be helpful in augmenting QoL while also lowering participants’ HbA1c level. The group intervention will consist of seven sessions of ACT and three follow-up sessions on glycaemic control and well-being.

## Methods/Design

### Study design and setting

The design of this study is a randomised wait-list controlled trial. The study will be conducted at Akademiska sjukhuset, Uppsala University Hospital, Uppsala.

### Participants and recruitment

Eighty patients aged 26–55 years with an HbA1c level >70 mmol/mol at the time of enrolment will be included. Exclusion criteria to the study will be ongoing severe depression, eating disorders or other severe mental illnesses, alcohol or substance abuse, or severe diabetes complications. Oral and written information about the present study will be given to patients who fulfil the inclusion criteria. Written informed consent or assent for participation in the study will be obtained from the participants.

### Randomisation

Participants who fulfil the inclusion criteria and are willing to participate in the study and have completed the pre-test will be randomly allocated to either the intervention or wait-list control group. A flow chart of the study is shown in Additional file 1.

### Intervention

The treatment is scheduled to run over a period of 6 months. Participants in the treatment condition will learn mindfulness and acceptance strategies to cope with diabetes-related distress. The treatment will focus on living according to one’s values and on behavioural activation. As the treatment is targeted towards a population with poorly controlled diabetes, the intervention will also include 1 week of measurements with a hidden continuous glucose monitoring system so that patients can see how their behaviour influences their blood glucose levels. All sessions will be led by a psychologist with specialisation in CBT and training in ACT, and a nurse specialised in diabetes. Each session will have an ACT-specific theme about how to promote psychological flexibility. The topics will include the acceptance of thoughts and feelings, and mindfulness. Exercises in mindfulness will be based in concrete practice, both during the course sessions and as homework. Acceptance will be practiced through experiential exercises, writing exercises and discussion. Each patient will commit to what is important for him or her to focus on in the next follow- up visit. The treatment session protocol is included in Additional file 2.

### Measures and data collection

Before starting ACT we will collect the following data from the participants: HbA_1c_ level, height, weight, insulin requirements, mean frequency of self-monitoring of blood glucose, Hospital Anxiety and Depression scale (HADS), ‘Check your health’ scale, and the Acceptance and Action Questionnaire 2 (AAQ2). These data will also be collected 6 and 12 months after starting ACT.

### HADS

The original HADS, which measures anxiety and depression, was developed by Zigmond and Snaith [23]. The HADS consists of 14 items, of which seven relate to anxiety and seven to depression. Responses are rated on a four-point Likert scale score (0–3), where 0 represents the lowest level of anxiety and depression and 3 the highest level. The Swedish version of HADS has been used in this study, which has been translated by Lisspers et al. [24].

### Check your health

‘Check your health’ measures perceived physical and emotional health, social relationships and general QoL on a vertical thermometer scales, ranging from 0 to 100, with 0 indicating low perceived health and QoL. Using the same scales, a person reports what their perceived physical and emotional health, social relationships and QoL would be if they did not have diabetes. The measured difference between, for example, physical health with and without diabetes is defined as the physical burden of diabetes. When the difference results in a positive value, meaning that, for example, imagined physical health without diabetes is reported to be lower than that with diabetes, the burden is interpreted as zero. In this study, the marginal values for no burden, low burden, high burden or very high burden will be arbitrary. ‘Check your health’ has been tested on adolescents and adults with diabetes and has shown good reliability and validity [25, 26].

### AAQ2

AAQ2 is a self-assessment questionnaire designed to measure psychological acceptance/flexibility and emotional avoidance, and how these two factors affect the individual’s freedom of action. The instrument includes 10 items in the form of statements that the respondent takes a position on in a seven-point Likert scale (1 = never true, 7 = always true), although seven of the 10 items are reversed (2, 3, 4, 5, 7, 8 and 9). Scores are calculated by summing the scores from the 10 items. Higher total values indicate a higher degree of flexibility [27].

### Statistical analysis and power calculation

To detect a difference of 6 mmol/mol in HbA1c (SD ± 11) at least 35 participants are needed in each group (power 80 % and alfa 0.05). In view of the drop-off, 80 patients will be included. The differences between the groups will be analysed with unpaired t-tests with 95 % confidence intervals and *p* < 0.05 considered as significant. Repeated- measures analysis of variance will be used for comparisons in the groups in pre- and post-measuring with the same confidence interval and level of significance. When testing differences between groups regarding AAQ2 and ‘Check your health’, the same statistical analysis will be used.

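### The stated inputs (6 mmol/mol, SD 11, 80% power, alpha 0.05) require 54 per group, not 35; power for the stated difference is 61% at 35 per group and 67% if all 80 are retained

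*Protocol article*

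**What the plan says.** The whole calculation is in one paragraph of the protocol article, in the section Statistical analysis and power calculation.

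- Target difference and variability: "To detect a difference of 6 mmol/mol in HbA1c (SD ± 11" mmol/mol).
- Error rates: "power 80 % and alfa 0.05".
- Result: "at least 35 participants are needed in each group".
- Allowance for losses: "In view of the drop-off, 80 patients will be included". No drop-out rate is given; 70 evaluable out of 80 implies 12.5%.
- Analysis between groups: "The differences between the groups will be analysed with unpaired t-tests", with 95% confidence intervals and significance at p < 0.05.

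Repeated-measures analysis of variance is also planned, for pre/post comparisons in the groups. The paragraph does not link it to the sample size. It gives no baseline correlation, no baseline adjustment and no one-sided test.

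**The concern.** The inputs, the test and the answer are all printed, so the answer can be checked without any other source. A standardised difference of 6/11, about 0.55, is of moderate size, and 35 per group is too few to detect it with 80% power in an unpaired comparison.

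HbA1c is the only outcome with a power calculation, and lowering it is half of the study aim. The Discussion presents the trial as filling a gap in type 1 diabetes. If the real power is well below 80%, a true 6 mmol/mol benefit would be missed far more often than the one time in five that the plan implies. A non-significant result could then carry more weight than it deserves, because readers would take the trial to be adequately powered. The enrolment target of 80 inherits the same error.

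**Working it through.** **Inputs**, all from the sample-size paragraph: difference Δ = 6 mmol/mol; SD σ = 11 mmol/mol; power 80%; alpha 0.05; unpaired t-test. Two assumptions are needed. Allocation is taken as 1:1, from the equal number required per group. The test is taken as two-sided, which the 95% confidence intervals paired with p < 0.05 imply.

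**1. Trying to reproduce 35.** The standardised difference is d = 6/11 = 0.545.

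- Normal approximation: n = 2(1.960 + 0.842)²(11/6)² = 52.8, so 53 per group.
- t distribution: n = 53.7, so 54 per group, or 108 evaluable in total against the 70 the plan relies on.

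**2. Other readings of the same inputs.**

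| Reading | n required |
|---|---|
| Two-sided unpaired, 80% power | 53 (normal), 54 (t) per group |
| One-sided unpaired, 80% power | 42 (normal), 43 (t) per group |
| Two-sided unpaired, 90% power | 71 (normal) per group |
| Paired or one-sample, two-sided, 80% power | 29 |
| Paired or one-sample, one-sided, 80% power | 23 |
| Paired or one-sample, two-sided, 90% power | 38 |

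None gives 35. Whether SD 11 describes the HbA1c level or its change makes no difference to the two-sample rows: whichever quantity is compared, its SD enters the same formula.

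**3. Power with the planned numbers** (unpaired t-test, Δ = 6, σ = 11).

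| Evaluable per group | Two-sided power | One-sided power | Difference detectable with 80% power (two-sided) |
|---|---|---|---|
| 35 | 61.4% | 73.0% | 7.5 mmol/mol |
| 40 (all 80 retained) | 67.3% | 78.0% | 7.0 mmol/mol |

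The risk of missing a true 6 mmol/mol difference is therefore 1 − 0.614 = 39% at 35 per group and 1 − 0.673 = 33% with no losses, against the 20% claimed.

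**4. What would make 35 correct.** With the t-test, 35 per group gives 80% power if the SD is 8.8 (with Δ = 6) or if the difference is 7.5 (with σ = 11). Neither matches the printed inputs.

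**5. Enrolment for the stated aim.** At the implied 12.5% loss, 108/(1 − 0.125) = 123.4, so 124 patients.

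**6. Baseline-adjusted analysis.** If 11 is the SD of the follow-up level and r is the correlation between baseline and follow-up, the effective SD under ANCOVA is 11√(1 − r²). The values of r are assumptions, because the document gives none. With 35 per group and Δ = 6:

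| r (assumed) | Power |
|---|---|
| 0.4 | 69% |
| 0.5 | 74% |
| 0.6 | 80% |
| 0.7 | 88% |

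**The case against.** The arithmetic is hard to dispute; the case on the other side concerns how much to conclude from it.

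*61% is the low end.* It applies only if the full implied 12.5% is lost, and the plan states no rate. With everyone retained, power is 67%. This is fair, and both figures should be quoted. Neither is near 80%.

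*There may be an unstated variance reduction.* The full protocol may have assumed one. An ANCOVA with a correlation of about 0.6 would give 35 per group, as would a change-score comparison with a correlation of about 0.67 if 11 is the SD of the level. This cannot be excluded, but the paragraph states no correlation and names a plain unpaired t-test. A fuller document could explain where 35 came from; it would not make the printed sentence correct.

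*Confidence intervals would show the imprecision.* They would, and this limits the harm to a careful reader. It does not correct the power claim.

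*ANCOVA is not a free remedy.* This objection stands. The table of correlations holds only if 11 is the SD of the follow-up level. If 11 is already the SD of change, the reduction cannot be applied to it in that way. Restricting entry to HbA1c above 70 mmol/mol also tends to lower the correlation. Picking 0.6 because it returns 35 would be working backwards from the answer.

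*The wrong input is unknown.* This also stands: the error may lie in the difference, the SD or the sample size, and the document does not show which.

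**Conclusion.** The concern holds. The stated sample size does not follow from the stated inputs: 54 per group are needed against 35 planned, so the evaluable total is 70 where 108 would be required, a shortfall of 38 patients or about 35%. Two-sided power for 6 mmol/mol is 61% at 35 per group and 67% if none of the 80 is lost.

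This rests on 1:1 allocation and a two-sided test. The second assumption is not critical, since a one-sided test at 0.05 still falls short at both 35 and 40 per group. It does not depend on whether SD 11 refers to the level or the change. It does rest on taking the printed 6, 11 and unpaired t-test at face value. This is the only sample-size justification in the document, so it should be corrected before the results are analysed.

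**What to change.** First, the sponsor should check the source of the difference, the SD and the sample size, and correct whichever was misprinted or miscalculated.

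If 6 and 11 stand, keep 80 patients and replace the sentence with, for example: *With 35 evaluable participants per group, a two-sided unpaired t-test at alpha 0.05 has 61% power to detect a difference of 6 mmol/mol in HbA1c (SD 11), or 80% power to detect 7.5 mmol/mol; if all 80 are retained, power for 6 mmol/mol is 67%.* This costs one rewritten sentence and a less favourable power statement.

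Alternatively, make baseline-adjusted ANCOVA the between-group analysis of HbA1c. State that 11 is the SD of the follow-up level (if it is), give the assumed correlation with its justification, and show power over a range such as 0.4 to 0.7. This changes the named analysis but needs no extra patients, provided that the correlation is about 0.6 or higher, or that lower power is accepted.

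Keeping 80% power for 6 mmol/mol with the plain t-test would instead require 108 evaluable patients, or about 124 enrolled at the implied 12.5% loss.

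### The between-group comparison is an unpaired t-test with no baseline covariate; adjusting for the baseline value would gain precision at no cost

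*Protocol article*

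**What the plan says.** The article's section 'Statistical analysis and power calculation' names the between-group test outright: "The differences between the groups will be analysed with unpaired t-tests", with 95% confidence intervals and a 0.05 significance level. No covariate is mentioned. The sentence that begins "When testing differences between groups regarding AAQ2" carries the same analysis over to AAQ2 and 'Check your health'. HADS is not named there. Repeated-measures analysis of variance is also planned, for pre- and post-measurement comparisons in the groups, which reads most naturally as within each group.

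The baseline values exist. Under 'Randomisation', participants who "have completed the pre-test will be randomly allocated" to one of the two arms. Under 'Measures and data collection', the sentence that begins "Before starting ACT we will collect the following data from the participants" lists HbA1c, HADS, 'Check your health' and AAQ2, and the same data are taken again at 6 and 12 months. The pre-test is not itemised, so it is an inference from these two sections, though a natural one, that each of these measures precedes allocation.

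The design figures are: "To detect a difference of 6 mmol/mol in HbA1c" with an SD of 11, "at least 35 participants are needed in each group" ("power 80 % and alfa 0.05"), and "In view of the drop-off, 80 patients will be included".

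**The concern.** A baseline value of the same measure usually predicts the follow-up value. In a randomised comparison, adjusting for it removes the part of the outcome variance that it explains. A t-test on final values leaves all of that variance in the error term. A t-test on change uses the baseline but fixes its coefficient at 1, which is generally not the best weight. Either way the confidence interval is wider than it need be.

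The trial is small, with 35 to 40 per group, and on its own inputs 35 per group does not give 80% power with an unadjusted t-test (shown below). Precision that is already paid for should not be left unused. At stake is the width of the interval for HbA1c, AAQ2 and 'Check your health'. The validity of the comparison is not in question.

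**Working it through.** **Inputs from the article:** difference 6 mmol/mol, SD 11, 35 per group, 80% power, alpha 0.05.

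**Assumptions:** a two-sided test, because 95% intervals are planned; 1:1 allocation; equal SDs at baseline and follow-up; r between 0.3 and 0.7, because the article gives no value; and two readings of SD 11, because the article does not say whether it describes the follow-up value or the change.

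**1. The plan's own figure.** For an unadjusted comparison, n per group = 2 × (11/6)² × (1.960 + 0.842)² = 52.8, so 53 by the normal approximation and 54 by the exact noncentral t. The stated 35 is not reproduced; a one-sided test would still need 42 (43 exact). With 35 per group the standard error is 11 × √(2/35) = 2.63, the standardised difference is 6/2.63 = 2.28, and two-sided power is 61% (exact t). With all 80 retained, 40 per group, it is 67%.

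**2. Reading A: SD 11 is the SD of the follow-up value.**

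- t-test on final values: SD 11, power 61% whatever r is.
- t-test on change: SD = 11 × √(2(1 − r)).
- ANCOVA: residual SD = 11 × √(1 − r²), with 67 degrees of freedom instead of 68.

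| r | change SD | power, change-score t-test | ANCOVA SD | power, ANCOVA |
|---|---|---|---|---|
| 0.3 | 13.02 | 48% | 10.49 | 65% |
| 0.4 | 12.05 | 54% | 10.08 | 69% |
| 0.5 | 11.00 | 61% | 9.53 | 74% |
| 0.6 | 9.84 | 71% | 8.80 | 80% |
| 0.7 | 8.52 | 83% | 7.86 | 88% |

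ANCOVA is ahead of both t-tests in every row. Against the final-value t-test the gain runs from about 4 points (r = 0.3) to 27 points (r = 0.7).

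**3. Reading B: SD 11 is the SD of change.** Then 2σ²(1 − r) = 121, where σ is the SD of a single value, so the ANCOVA variance is σ²(1 − r²) = 121 × (1 + r)/2. The t-test on change has 61% power.

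| r | ANCOVA SD = 11 × √((1 + r)/2) | power, ANCOVA | power, t-test on change |
|---|---|---|---|
| 0.3 | 8.87 | 80% | 61% |
| 0.4 | 9.20 | 77% | 61% |
| 0.5 | 9.53 | 74% | 61% |
| 0.6 | 9.84 | 71% | 61% |
| 0.7 | 10.14 | 68% | 61% |

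Here the gain shrinks as r rises, the reverse of the pattern against the final-value t-test in reading A, but it stays positive: about 18 points at r = 0.3 and 7 at r = 0.7.

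**4. What adjustment does not do.** Under reading A, 35 per group reaches 80% power only if r is about 0.60 or more (exact t), and 40 per group only if r is about 0.51 or more. Under reading B, 35 per group reaches about 80% at r = 0.3 and falls below it as r rises.

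**The case against.** The strongest reply is that nothing here is invalid. Under randomisation the unpaired t-test is unbiased, and its interval already allows for chance differences at baseline. That stands.

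Four stronger readings are tempting, and the article does not support them.

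- **That the group comparison ignores baseline.** The article does not say whether the t-test is on final values or on change, and the Discussion speaks of determining changes. The repeated-measures analysis could also be meant as a group-by-time test; with two time points that is equivalent to the change-score t-test. These readings use the baseline, but less efficiently than ANCOVA, so the recommendation survives them.
- **That chance imbalance in baseline HbA1c carries over in full to the estimated effect.** With final values it carries over only in proportion to the slope of outcome on baseline. If the baseline SD is also 11, the standard error of the baseline difference is 2.63 mmol/mol, of which the fraction r would pass through when the SDs are equal.
- **That partly observed patients are discarded.** A t-test at a given visit uses every value observed at that visit, and ANCOVA at 6 months would recover nobody who lacks a 6-month value. How the repeated-measures analysis treats missing visits is a matter a full analysis plan may settle.
- **That adjustment rescues the sample size.** It does so only for some values of r, as shown above. The figure of 35 per group is a separate error.

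The size of the gain is also uncertain. Entry restricted to HbA1c above 70 mmol/mol may lower r, and at r = 0.3 under reading A the gain over a final-value t-test is only about 4 points.

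**Conclusion.** The point holds as a matter of efficiency. The article fixes an unpaired t-test without a covariate for HbA1c, AAQ2 and 'Check your health', when a baseline-adjusted comparison is available from data it already plans to collect. ANCOVA has more power than the t-test on final values or on change at every r from 0.3 to 0.7 if 11 is the SD of the follow-up value, and more than the t-test on change if 11 is the SD of change. With 35 per group its power is 65% to 88% on the first reading and 80% down to 68% on the second, against 61% for an unadjusted t-test with SD 11. The direction is secure. The size rests on an assumed r, on an unstated meaning of SD 11 and on equal SDs at the two times. The arithmetic concerns HbA1c only: the article gives no design figures for the questionnaires, for which the same argument holds in kind.

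**What to change.** In 'Statistical analysis and power calculation', replace the unpaired t-test by ANCOVA of the follow-up value on randomised group and the baseline value of the same outcome, for HbA1c, AAQ2 and 'Check your health'. Report the adjusted mean difference with its 95% confidence interval as the main between-group result. State also whether SD 11 is the SD of the follow-up value or of the change, so that the expected gain can be judged.

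The cost is a change of wording and one degree of freedom; no new data, visits or patients are needed. It should be settled before outcome data are examined by group. The stated 35 per group needs its own correction and should not be treated as repaired by this change.

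### ACT is given in groups, but the planned unpaired t-tests make no allowance for therapy group; if outcomes correlate within groups, p-values are too small and confidence intervals too narrow

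*Protocol article*

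**What the plan says.** The Study aim section describes the treatment as group-based: "The group intervention will consist of seven sessions of ACT and three follow-up sessions on glycaemic control and well-being". Under Intervention, much of the content is shared work in the sessions, such as mindfulness practice, experiential exercises and discussion. On staffing, that section says: "All sessions will be led by a psychologist with specialisation in CBT and training in ACT, and a nurse specialised in diabetes". The Randomisation section allocates patients, not groups; they "will be randomly allocated to either the intervention or wait-list control group".

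The section Statistical analysis and power calculation fixes the between-arm test, to be reported with 95% intervals: "The differences between the groups will be analysed with unpaired t-tests". For AAQ2 and 'Check your health' it adds that "the same statistical analysis will be used". It also names repeated-measures analysis of variance for pre/post comparisons. The sample size is 35 per group for a difference of 6 mmol/mol (SD 11), raised to 80 patients in all. The article nowhere mentions therapy group as a factor, an ICC or a design effect, in the analysis or the sample size.

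**The concern.** Individual randomisation with group delivery in one arm gives a partially nested design. Patients who attend the same sessions with the same peers may end up more alike than patients from different groups. The mean of the ACT arm then varies more than its patient-level standard deviation suggests, and the unpaired t-test does not see the extra variance. The error runs one way: the null is rejected too often, whether the effect is zero or small. HbA1c is exposed, and so are AAQ2 and 'Check your health', self-reports that group discussion could plausibly influence.

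**Working it through.** **Inputs from the article.** Difference 6 mmol/mol, SD 11, alpha 0.05, power 80%, 35 per group, 80 enrolled (40 per arm if allocation is 1:1). Two-sided testing is taken as the default because sidedness is not stated.

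**Assumed.** Therapy groups of 8 (6 to 12 as a range), ICC 0 to 0.10, and ungrouped wait-list patients.

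**Step 1: the plan's own figure, with independent patients.** n per arm = 2 × (11 × (1.960 + 0.842) / 6)² = 2 × 26.38 = 52.8, so 53. A one-sided test needs 42. Neither is 35. At 35 per arm the standard error is 11 × √(2/35) = 2.63, so power is Φ(6/2.63 − 1.96) = Φ(0.32), about 63%. At 40 per arm it is about 68%. This shortfall exists without any clustering.

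**Step 2: effect of clustering on the planned test.** The variance of the ACT mean is multiplied by DEFF = 1 + (m − 1) × ICC, and the control arm is unchanged. The true standard error over the one the t-test uses is therefore about √((DEFF + 1)/2), and type I error is about 2 × (1 − Φ(1.96 / ratio)). With m = 8, and simulation of the t-test at 40 per arm (100,000 trials per setting):

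| ICC | DEFF | SE ratio | Type I, formula | Type I, simulated |
|---|---|---|---|---|
| 0 | 1.00 | 1.000 | 5.0% | 4.9% |
| 0.01 | 1.07 | 1.017 | 5.4% | 5.3% |
| 0.02 | 1.14 | 1.034 | 5.8% | 5.8% |
| 0.05 | 1.35 | 1.084 | 7.1% | 7.1% |
| 0.10 | 1.70 | 1.162 | 9.2% | 9.1% |

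At ICC 0.05 and 0.10 the nominal 95% interval covers about 92.9% and 90.9%. For groups of 6 to 12 (36 to 40 per arm), simulated type I error is 6.4% to 8.4% at ICC 0.05 and 7.9% to 11.8% at ICC 0.10.

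**Step 3: what a valid test gives.** A test of therapy-group means against individual controls, with Satterthwaite degrees of freedom, was simulated for five groups of 8 and 40 controls:

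| ICC | Type I | Power at 6 mmol/mol | Rejection rate of the planned t-test at 6 mmol/mol |
|---|---|---|---|
| 0 | 5.0% | 62% | 68% |
| 0.05 | 5.4% | 54% | 66% |
| 0.10 | 5.4% | 48% | 66% |

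The planned test hardly loses rejections as the ICC rises; its fault is its size.

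**Step 4: sample size.** With n per arm = (DEFF + 1) × 26.38 and m = 8, 80% power needs 53 at ICC 0, 55 at 0.01, 62 at 0.05 and 72 at 0.10.

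**The case against.** The strongest reply is that nothing in the article shows a positive ICC. It gives no ICC, group size or number of groups, and the session protocol is in an additional file that is not shown. At ICC 0.01 the type I error is about 5.4%, which nobody would act on. This stands: the point is conditional, and a reader should not infer that the trial's p-values are certainly wrong.

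Three stronger readings also fail.

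- **Power.** A reader might set the 54% or 48% above against the plan's 80% and blame clustering. Those figures belong to a corrected test at 40 per arm, where even independent patients give only about 68%. Part of the remaining gap is the price of few degrees of freedom: the group-means test has 62% at ICC 0. The drop from 80% comes first from the sample size error in Step 1.
- **Leaders.** Shared leaders might seem to prove correlation. If one psychologist and one nurse lead every group, their effect is constant across the ACT arm and adds no between-group variance. Only shared sessions and peers then remain as sources.
- **Controls.** The article does not say whether or when wait-list patients receive group ACT, so they cannot be taken as ungrouped at 12 months.

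It might also be said that clustering belongs in an unseen statistical analysis plan. That does not answer the point, because the article itself names the between-arm test, and an unpaired t-test has no place for a therapy-group term.

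**Conclusion.** The point holds in conditional form. The article fixes an analysis that assumes independent patients for a treatment given in groups, and makes no allowance for therapy group in the test or the sample size. For any positive within-group correlation the planned test rejects too often and its intervals are too narrow.

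The size cannot be read from the documents. Under the assumed 40 per arm and groups of 8, type I error runs from 5% (ICC 0) through about 5.4% (0.01) and 7% (0.05) to 9% (0.10). The distortion is negligible to moderate: worth correcting, but not grounds for calling the design invalid. The failure of 35 per group to give 80% power is a separate error.

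**What to change.** Record the therapy group of each ACT patient. Replace the unpaired t-test with a partially nested mixed model: a random therapy-group effect in the ACT arm, controls as singletons, and Satterthwaite or Kenward-Roger degrees of freedom. A test on therapy-group means with Satterthwaite degrees of freedom is an acceptable equivalent. Use the same approach for AAQ2 and 'Check your health'. If wait-list patients receive group ACT before the 12-month visit, model their grouping at that visit too. Report the ICC with its uncertainty, and state that the sample size makes no allowance for clustering.

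The change needs one data field and one model term, and leaves randomisation, treatment and visits as they are. The article describes the study as ongoing, so membership is best captured now.

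The statistical cost is real. Intervals widen, and at 40 per arm the group-means test has about 62%, 54% and 48% power at ICC 0, 0.05 and 0.10, against about 68% for a t-test with truly independent patients. With four or five groups the ICC will be imprecise and may often be estimated as zero. With very few groups the repair is incomplete: with three groups of 12 (36 per arm), the group-means test had type I error of about 6.3% and 6.5% at ICC 0.05 and 0.10, still better than 8.4% and 11.8% for the planned test.
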